## 4.2.2 Research Questions

1. What is the knowledge base of health workers regarding pre-intra and postnatal care
2. What is the perception of healthcare workers towards the provision of individual prenatal education to pregnant women

## 4.2.3 Objectives

### 4.2.4 General

To assess the knowledge and perception of primary healthcare workers regarding prenatal educational interventions offered during ANC care; understand the factors contributing to poor implementation of the comprehensive care model with the aim of designing an intervention that will engage a team of CHWs to offer individual prenatal educational interventions to pregnant women.

### 4.2.5 Specific

1. Determine the knowledge of Primary Healthcare workers regarding preventive and promotional interventions offered to pregnant women and newborn babies during the pre-and neo-natal period
2. Assess the perception of primary healthcare workers regarding CHWs offering a combined package of prenatal educational interventions and using mobile phone reminders to pregnant women during ANC clinics
3. Explore the modality of engaging a team of Community Health Workers to offer prenatal educational interventions to pregnant women at the primary care facility

# 4.2.6 Methodology

This study will be done in Masindi and Kiryandongo districts. The study design will be a descriptive exploratory cross-sectional study design employing qualitative and quantitative data collection techniques. Respondents will be health managers and health workers routinely involved in offering prenatal care to pregnant women and newborns at the primary care level (Health Centres II, III, IV and ANC clinics of the hospitals) in the districts of Masindi and Kiryandongo. The study unit of analysis will be individual health workers. In the quantitative survey, we will administer questionnaires with Multiple-Choice-Questions adapted from ([Bhutta, Darmstadt et al. 2005](#_ENREF_13); [Leif E, Nguyen T et al. 2009](#_ENREF_53)) to a total of 132 nursing assistants, nurses and midwives who are routinely engaged in providing ANC and newborn care services at the primary care facilities in the two districts of Masindi and Kiryandongo. This questionnaire makes assessment for four major aspects of maternal and newborn care: Antenatal, intra-natal, postnatal and follow-up visits in the community. These questionnaires will be administered by the PI to all eligible health.

For the qualitative technique we will conduct up to 20 Key-Informant Interviews with stakeholders at the health facility using a pre-designed interview guide (*details of guide in annex 3*). Five health managers from each district will be recruited for the interview. These respondents will be purposively selected given their specific role as health managers (*list of respondents see annex 4*)

## 4.2.7 Sample size

Preliminary assessments indicate that the staffing level for nurses, midwives and nurse assistants in the two districts could stands at about 200 staffs. The sample size calculation will be estimated using the formulae for cross-sectional studies [$Z^{2}$PQ]/$\delta^{2}$]; substituting the formula-assuming a health worker knowledge of **50%**, with a sampling error of **9%** an estimated sample size of 120 health workers will be recruited. Considering a 10% non response we obtain a sample size of 132 health workers. All midwives working in the two districts, all nurses and nursing assistant in health centres II, III and IV and nurses working in the outpatients and children’s wards will be eligible to participate in the study. A total of 132 health workers from both districts will be randomly selected. A list of all health workers providing services in the two districts will be obtained from their respective health sub districts and stratified by the different cadres (Nursing assistants, nurses and midwives) and a proportionate number will be sampled. For both the quantitative and qualitative studies health workers will be visited in their respective health centres and data will be collected by the Principal Investigator.

## 4.2.8 Study variables

- Perceptions of health workers about comprehensive maternal and newborn care
  - Provision of technical ANC services for example taking and recording BP, weight, screening for HIV integrated with,
  - Provision of less technical and more promotional services mainly health education
- Perception of health workers about working with Community Health Workers
- Knowledge of health workers about pre-natal care
  - Dietary requirement for pregnant women
  - Danger signs during pregnancy
  - Birth preparation
- Knowledge of health workers about neo-natal care
  - Hygiene and cord care
  - Warmth for the newborn
  - Early initiation and exclusive breast feeding
  - Recognition of danger signs

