# Chapter Four

# Study Methodology

## 4.1 Study site and population

The study will be done in the two districts of Masindi and Kiryandongo in western Uganda, 214 kilometres northwest of Kampala the capital city of Uganda. It is bordered by Amuru district in the north; Oyam to the northwest; Apac in the South; Hoima to the southwest and Bulisa in the Northwest. It is administratively divided in to three counties (Buruli, Kibanda and Bujenje); eight sub counties and 40 parishes. The district population is projected to be 603,000 inhabitants by 2010, 50.9% being male and 49.1% female. Its inhabitants are of heterogeneous ethnicity and nationality; the Banyoro comprising about 59%. The population is predominantly rural with about 5.43% being urban. It has a population density of 124 per square kilometres.

There are two general Hospitals and one sub district hospital, Masindi, Kiryandongo and Bwijanga respectively; 16 health centre III levels and; 26 health centre II levels (Masindi having 25 health centres while Kiryandongo has 17. In this region ANC new attendance is 89.4%; ANC fourth visit is 29.4%; IPT_2_ at 27.2% and Health facility deliveries in this region is 23.5% ([DHO 2010](#_ENREF_28)).

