### ****4.2.11 Sub study one-Summary of methodology****

| **Objectives** | **Methods** | **Indicator/data to be collected** | **Target population** | **Sample size** |
| --- | --- | --- | --- | --- |
| 1. **1.** Determine the knowledge of Primary Healthcare workers regarding preventive and promotional interventions offered to pregnant women and newborn babies during the pre-and neo-natal period | **Structured Interviews** | **Knowledge of health workers regarding pre-and neo-natal prevention and promotional intervention** | **Health workers routinely engaged in providing pre-and neo-natal health** | **Random sampling (132 health workers)** |
| **2.** Assess the perception of primary healthcare workers regarding the provision of individual prenatal educational interventions to pregnant women during ANC clinics   1. **3.** Explore the modality of engaging a team of Community Health Workers to offer individual prenatal educational interventions to pregnant women at the primary care facility | **Key-Informant Interviews** | **Perception of stakeholders** | **DHO, MS, PNO, manager for maternity unit of hospital, manager for Community health Department of hospitals, and manager for ANC clinic of hospital** | **Purposive sampling up to 20 stakeholders (health managers and health care providers) from Masindi and Kiryandongo** |

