**Which level of healthcare are you currently working in?**

1. Hospital

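### Sub-study one's questionnaire (Annex 1) does not measure two of the seven knowledge variables in section 4.2.8, maternal diet and recognition of newborn danger signs; it also asks nothing about the woman in labour and has no HC II code

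*Protocol*

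**What the plan says.** Section 4.2.8 sets out what sub-study one will measure. Under prenatal knowledge it lists "Dietary requirement for pregnant women", danger signs of pregnancy and birth preparation. Under neonatal knowledge it lists hygiene and cord care, warmth, breastfeeding and "Recognition of danger signs".

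Section 4.2.6 describes the tool: "This questionnaire makes assessment for four major aspects of maternal and newborn care: Antenatal, intra-natal, postnatal and follow-up visits in the community". Research question 1 in section 4.2.2 likewise asks about knowledge before, during and after birth. The summary in section 4.2.11 assigns the knowledge objective, "Knowledge of health workers regarding pre-and neo-natal prevention and promotional intervention", to structured interviews. Annex 1, labelled for sub-study one, is therefore the instrument that has to carry these variables.

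On who answers it, section 4.2.6 takes in "Health Centres II, III, IV and ANC clinics of the hospitals", and section 4.2.7 makes eligible "all nurses and nursing assistant in health centres II, III and IV". Annex 1 asks "Which level of healthcare are you currently working in" and offers hospital, HC IV and HC III.

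Section 4.2.10 reports the proportion of workers who reach a minimum score, with scores stratified by cadre, and expects the results to show where knowledge is lacking.

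**The concern.** A knowledge variable can be reported only if something on the form measures it. Here the protocol fixes both the variables and the form, and the two do not match. This is not a detail that an analysis plan could supply later, because an item that was never asked cannot be recovered in analysis.

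At stake is sub-study one's answer to its own knowledge objective. A single score presented as covering prenatal and neonatal knowledge would contain nothing on diet in pregnancy and nothing on recognising a sick newborn. A reader of the results could take the absence of a reported gap in these topics as evidence that there is none.

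**Working it through.** The check is one of content. The only calculated figure for sub-study one is its sample size: 1.96² × 0.5 × 0.5 / 0.09² = 118.6, against 120 stated, and 120 × 1.10 = 132 as stated. That is consistent, and nothing below depends on it.

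**Variables in section 4.2.8 against items in Annex 1**

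| Listed variable | Where Annex 1 touches it | Measured? |
| --- | --- | --- |
| Diet in pregnancy | No item. The item on information to discuss with the woman does not offer diet as an answer. Increased appetite appears only as an answer option in the pregnancy danger-sign item. | No |
| Danger signs in pregnancy | Prenatal care: one item | Yes |
| Birth preparation | Prenatal care: an answer option in the item on information to discuss | Yes, thinly |
| Hygiene and cord care | Infection management: cord items | Yes |
| Warmth | Temperature/low birth weight: one item on stabilising temperature | Yes |
| Breastfeeding | Breastfeeding: four items | Yes |
| Recognition of newborn danger signs | See below | No |

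Result: 2 of 7 variables have no item.

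**Newborn danger signs.** The only item that asks for danger signs concerns pregnancy. Three others come close:
- The item on a baby unwell at birth (Immediate postnatal care) describes the healthy signs in the question and asks how to care for a baby lacking them.
- The item on an abnormal cord (Infection management) names the signs and asks how to handle them.
- The item on why home visits matter (Home visits) offers answers that mention feeding, stools, cord, icterus, skin and temperature as things to ask about or examine.

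The first two test management. The third tests the purpose of a visit. None asks the worker which signs mean danger.

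**Intra-natal care.** Annex 1's knowledge blocks are prenatal care, breastfeeding, immediate postnatal care, infection management, temperature/low birth weight and home visits. Newborn care around birth does appear: cord cutting, care of a baby unwell at birth and prevention of eye infection. Items on care of the woman in labour: 0.

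**Level of care.** The codes run 1 to 3 (hospital, HC IV, HC III) and go straight on to the department question. There is no HC II code and no other-level option. Section 4.1 counts 16 level III centres and "26 health centre II levels", so level II makes up 26 / (16 + 26) = 61.9% of the centres counted there. This is a share of centres; the protocol does not give the share of respondents.

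**The case against.** Several points on the other side are fair.

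- **The trial's education.** A reader might infer that the gap would distort the intervention. The documents do not support that. Section 4.4.1 has the health-worker study inform how antenatal services are re-oriented and takes the educational messages from the community survey. That survey's own tool (Annex 6) asks about forbidden foods and how newborn illness was noticed, and Annex 15 already contains diet and recognition of a sick child. The Abstract says only in general terms that both formative studies inform sub-study three.
- **HC II.** A reader might infer that about 62% of respondents would be miscoded, or that results would be biased. The percentage counts centres, not staff, and leaves out the hospitals. Staff are sampled by cadre, scores are stratified by cadre only, and the investigator visits workers at their own centres. No planned analysis uses the level code.
- **Intra-natal coverage.** It would be too strong to say that the topic is absent or rests on the cord item alone. Three newborn items concern the time around birth, section 4.2.6 promises aspects and not separate sections, and objective 1 in section 4.2.5 covers only the prenatal and neonatal periods. What stands is that sections 4.2.2 and 4.2.6 claim more than is asked.
- **Newborn signs.** The home-visit item does touch the subject, so the form is not wholly silent on newborn illness. It still does not test recognition, which is the variable listed.
- **Pretesting.** Section 4.2.9 provides for two pretests and adjustment. That is a route for repair, but the stated purpose is suitability, with no commitment to compare content with section 4.2.8.

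The interview guides in Annexes 2 and 3 probe feeding advice and clean delivery, but they produce no knowledge score.

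**Conclusion.** The mismatch is real and limited. As written, Annex 1 leaves 2 of the 7 listed knowledge variables unmeasured, supports the intra-natal claim only on the newborn side, and lacks a response code for one eligible level of facility. The harm falls on formative sub-study one, whose score and account of knowledge gaps would say nothing about diet in pregnancy or recognition of newborn danger signs. The HC II omission is a miscoded descriptor and no more. The trial's primary outcomes, sample size and analysis are untouched.

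This rests on two readings: that Annex 1 is the full questionnaire meant in section 4.2.6, and that recognition means the worker identifying the signs and not managing signs already named. It is worth correcting because the repair is easy before fieldwork and impossible after it.

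**What to change.** Before the planned pretests:

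1. Add to Annex 1 at least one item on diet in pregnancy.
2. Add at least one item that asks the worker to identify newborn danger signs.
3. Add HC II to the level-of-care codes.
4. Either add intra-natal items, or reword sections 4.2.2 and 4.2.6 to the newborn care around birth that is actually asked.

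If the items under 1 and 2 are not added, remove those two variables from section 4.2.8 and do not report on them.

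The cost is a few items on a form already due to be pretested twice, and a slightly longer interview. Sample size and sampling do not change.

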## 4.2.9 Data collection

The PI will administer both qualitative and quantitative questionnaires to eligible health workers.

A double data entry will be made in to epidata version 3.02 computer program, checked, cleaned and exported to stata version 10.0 for analysis.

Data will be transcribed verbatim and analysed for major themes and emerging sub themes using NVivo computer software program. All data collection tools will be pretested twice for suitability and necessary adjustments done prior to field interventions. Written informed consent will be obtained from all participants in the study.

## 4.2.10 Data analysis plan

Quantitative data will be analysed and presented as descriptive statistics in terms of proportions of health workers who will obtain a minimum acceptable score; a second part will stratify scores according to the different health cadres for comparison purposes. We will capture the unique health workers’ perspectives towards provision of individual educational interventions for prenatal women by the health workers on the one hand and by CHWs on the other. Meanwhile for the qualitative data contents will be analysed and presented according emerging themes and these will be used to triangulate with the quantitative information gathered.

Results from this study will illuminate knowledge gaps and major implementation challenges with delivering educational and counselling interventions to prenatal women during ANC at the primary care facilities. It will further provide information on alternative ways of engaging community health workers in the provision of educational interventions at the primary care level. And finally it will suggest ways of utilising mobile phones to enhance return prenatal visits, increase institutional deliveries and improve newborn homecare practices.

### ****4.2.11 Sub study one-Summary of methodology****

| **Objectives** | **Methods** | **Indicator/data to be collected** | **Target population** | **Sample size** |
| --- | --- | --- | --- | --- |
| 1. **1.** Determine the knowledge of Primary Healthcare workers regarding preventive and promotional interventions offered to pregnant women and newborn babies during the pre-and neo-natal period | **Structured Interviews** | **Knowledge of health workers regarding pre-and neo-natal prevention and promotional intervention** | **Health workers routinely engaged in providing pre-and neo-natal health** | **Random sampling (132 health workers)** |
| **2.** Assess the perception of primary healthcare workers regarding the provision of individual prenatal educational interventions to pregnant women during ANC clinics   1. **3.** Explore the modality of engaging a team of Community Health Workers to offer individual prenatal educational interventions to pregnant women at the primary care facility | **Key-Informant Interviews** | **Perception of stakeholders** | **DHO, MS, PNO, manager for maternity unit of hospital, manager for Community health Department of hospitals, and manager for ANC clinic of hospital** | **Purposive sampling up to 20 stakeholders (health managers and health care providers) from Masindi and Kiryandongo** |

# 4.3 Sub-study two

**Prevalence of common pre-and neo-natal homecare practices their rationale and determinants among communities of Masindi and Kiryandongo districts in Western Uganda**

## 4.3.1 Introduction

Homecare givers for maternal and newborns very often engage in potentially harmful practices like applying substances on the cord, providing pre-lacteal feeds to the newborn and other unhygienic practices ([Ingunn M, Wamani H et al. 2007](#_ENREF_43); [Kesterton and Cleland 2009](#_ENREF_47); [Waiswa P, Stefan P et al. 2010](#_ENREF_99)). Moreover health seeking behaviours for maternal, child and newborn services in sub Saharan Africa remains very low and erratic ([WHO/UNICEF 2009](#_ENREF_115); [King R, Mann V et al. 2010](#_ENREF_49)).

Low uptake of services aggravated by delay in seeking for care significantly compromise maternal and neonatal survival outcomes leading to preventable deaths ([Bazzano A, Kirkwood B et al. 2008](#_ENREF_9)). Maternal and newborn care practices in the community are deeply rooted in tradition and myths surrounding pregnancy and neonates ([Damstadt G, Uzma U et al. 2006](#_ENREF_23); [Bazzano A, Kirkwood B et al. 2008](#_ENREF_9); [Kesterton and Cleland 2009](#_ENREF_47)).

Behaviour change and health seeking in relation to maternal and newborn health is pivotal in morbidity and mortality reduction strategies ([Bhutta, Darmstadt et al. 2005](#_ENREF_13); [Wade A, Osrin D et al. 2006](#_ENREF_95)). Successful implementation of educational intervention packages therefore requires in depth knowledge of prevalent pre-and neo-natal homecare practices within the local context and their influences on maternal and newborn care and care-seeking behaviour ([Bhutta, Darmstadt et al. 2005](#_ENREF_13); [Kesterton and Cleland 2009](#_ENREF_47)).

This study is specifically designed to explore and quantify common homecare practices, their rationale and determinants; analyse their harmful or beneficial characteristics and highlight areas for change or enhancement to inform the individual prenatal educational intervention strategies planned during ANC at the primary care level. While similar studies have been done elsewhere in Uganda ([Waiswa P, Peterson S et al. 2010](#_ENREF_98)), they site limitations related to the small and homogenous population in the Demographic and Health Surveillance Site (DHSS) where these studies were conducted. Our study will be conducted in Masindi and Kiryandongo with a diverse ethnic composition.

# 4.3.2 General objective

To understand the common pre-and neo-natal homecare practices; determine their magnitude, identify those potentially harmful and healthy practices in order to inform the future educational intervention offered to pregnant women at the primary care level.

## 4.3.3 Specific objective

1. Determine the common pre-and neo-natal homecare practices and their determinants among lactating women in Masindi and Kiryandongo districts
2. Investigate the rationale for the different homecare practices offered to pregnant women and newborn babies during the pre-,intra- and immediate post-natal period in the districts of Masindi and Kiryandongo
3. Explore homecare experiences received by lactating women during the pre-and neo-natal period in the district of Masindi and Kiryandongo

##

## 4.3.4 Methodology

This will be a cross-sectional population-based survey among lactating women, Traditional Birth Attendants and elderly caregivers. Data collection techniques will include Structured and In-Depth Interviews with lactating mothers, Key Informant Interviews with elderly care givers and Traditional Birth Attendants (TBAs).

The Key Informant Interviews with elderly care givers and TBAs will precede the structured interviews with lactating mothers so that new emerging themes can be incorporated in to the structured interview with lactating mothers. Elderly care givers and TBAs will be purposively identified based on their routine engagement in the provision of pre-and neo-natal care services to individual women in the communities.

### 4.3.5 Sample size and technique

The formulae for cluster surveys will be used to estimate the maximum number of clusters and sample size. Using the formula,

C= [Z^2^PQ] D/$\delta^{2}b]$ Where,

- Z, the standard normal deviate at 95% confidence which is 1.96
- P, the prevalence of homecare practices in the region taken to be 42% (0.42) [good cord care ([Waiswa P, Stefan P et al. 2010](#_ENREF_99))]
- Q, (1-p) is 0.58
- D, the design effect taken to be 2,
- $\delta$, a sample error of 5%
- b, the average number of individuals to be sampled per cluster = 40 (derived from 4.85% of expected deliveries per population),

Substituting, the number of clusters needed for the survey is 18.7, implying that a minimum sample size of 748; adjusted for 10% non response we will recruit 823 participants from 21 clusters (see annex 5).

### 4.3.6 Sampling procedure

For the quantitative survey, clusters will be stratified at the parish level; a list of all parishes will be obtained from the planning unit of the districts and 21 of them will be selected by a simple random technique using computer generated random numbers. At the parish level all lactating women with babies up to four months will be enumerated and a list generated. From this list a random sample proportionate to the total number will be identified and included in to the study. A written consent will be obtained from each participating lactating woman. Structured interview questionnaire (*see annex 6 for details*) will be administered by trained research assistants to all lactating women who provide consent to participate in the study.

This study will be conducted in Masindi and Kiryandongo districts in western Uganda. The questionnaire guide will be pre-tested twice to ensure suitability.

In the qualitative study, six elderly caregivers and six traditional birth attendants will be identified with the help of Local council I chairpersons or their representative from any of the 21 parishes sampled. Thirty lactating mothers stratified by age groups (adolescents 10-20 years and adults above 20 years) will be selected for In-Depth Interviews. All these will be individual interviews with open-ended questions. Written informed consent will be obtained from participants and the interview administered on acceptance (*see annex 7 for details of question guide)*. While we plan to interview a total of six elderly care givers and six TBAs the absolute number will be determined when we arrive at saturation point-when no more new practices and explanations are volunteered in subsequent interviews.

For the quantitative survey, lactating mothers having babies up to sixty days old (about two months) will be eligible for the study (see annex 5 for sampling procedure). The unit of analysis will be individual lactating mothers.

The number of lactating mothers to be interviewed per cluster will be allocated proportionate to the number of eligible lactating mothers available in the selected parishes.

Eligible lactating mothers will be identified by the use of village-bicycle scouts assisted by the local council I chairpersons (LC I) who will enumerate all eligible lactating mothers and generate a list; from this list a proportionate number from each of the parishes will be sampled using a simple random selection technique.

